## LIST OF ABBREVIATIONS AND RELEVANT DEFINITIONS

|         |                                                                                                                                                                                                                                                                                                                                           |
|---------|-------------------------------------------------------------------------------------------------------------------------------------------------------------------------------------------------------------------------------------------------------------------------------------------------------------------------------------------|
| ABR     | ABR form (General Assessment and Registration form) i.e. the application form required for submission to the accredited Ethics Committee (ABR = Algemene Beoordeling en Registratie)                                                                                                                                                      |
| AE      | Adverse Event                                                                                                                                                                                                                                                                                                                             |
| AR      | Adverse Reaction                                                                                                                                                                                                                                                                                                                          |
| CA      | Competent Authority                                                                                                                                                                                                                                                                                                                       |
| CCMO    | Central Committee on Research Involving Human Subjects                                                                                                                                                                                                                                                                                    |
| CV      | Curriculum Vitae                                                                                                                                                                                                                                                                                                                          |
| DSMB    | Data Safety Monitoring Board                                                                                                                                                                                                                                                                                                              |
| EU      | European Union                                                                                                                                                                                                                                                                                                                            |
| EudraCT | European drug regulatory affairs Clinical Trials                                                                                                                                                                                                                                                                                          |
| GCP     | Good Clinical Practice                                                                                                                                                                                                                                                                                                                    |
| IB      | Investigator's Brochure                                                                                                                                                                                                                                                                                                                   |
| IC      | Informed Consent                                                                                                                                                                                                                                                                                                                          |
| IMP     | Investigational Medicinal Product                                                                                                                                                                                                                                                                                                         |
| IMPD    | Investigational Medicinal Product Dossier                                                                                                                                                                                                                                                                                                 |
| METC    | Medical research ethics committee (MREC); in Dutch: medisch ethische toetsingscommissie (METC)                                                                                                                                                                                                                                            |
| (S)AE   | (Serious) Adverse Event                                                                                                                                                                                                                                                                                                                   |
| SPC     | Summary of Product Characteristics (in Dutch: officiële productinformatie IB1-tekst)                                                                                                                                                                                                                                                      |
| Sponsor | The sponsor is the party that commissions the organization or performance of the research, for example a pharmaceutical company, academic hospital, scientific organization or investigator. A party that provides funding for a study but does not commission it is not regarded as the sponsor, but referred to as a subsidizing party. |
| SUSAR   | Suspected Unexpected Serious Adverse Reaction                                                                                                                                                                                                                                                                                             |
| WBP     | Personal Data Protection Act (in Dutch: Wet Bescherming Persoonsgegevens)                                                                                                                                                                                                                                                                 |
| WMO     | Medical Research Involving Human Subjects Act (Wet Medisch-wetenschappelijk Onderzoek met Mensen)                                                                                                                                                                                                                                         |

## **SUMMARY**

### **Rationale:**

Cardiovascular disease is the leading cause of mortality in patients with end-stage renal disease (ESRD). The vascular abnormalities in ESRD are especially characterized by arterial wall calcifications, whereas intimal hyperplasia seen with "classic atherosclerosis" is less pronounced. These calcifications are strongly associated with increased mortality. The exact mechanism by which calcification develops is unknown, but there is a direct relationship with increased serum calcium and serum phosphorus. With long and frequent hemodialysis, such as nocturnal hemodialysis, and with renal transplantation, calcium and phosphate levels can be normalized. It is unknown whether these treatments inhibit the progression of arterial calcification or bring about regression of calcification. The hypothesis of this study is that with nocturnal hemodialysis the progression of arterial calcification is less than with conventional hemo- or peritoneal dialysis, and approximates the progression rate seen with a renal transplant.

### **Objective:**

1. To assess whether nocturnal hemodialysis and renal transplantation are associated with less progression of coronary arterial calcification, compared with conventional hemodialysis and peritoneal dialysis;
2. To identify risk factors for coronary arterial calcification in dialysis and transplant patients, and to assess a possible interaction with treatment modality.

### **Study design:**

Prospective observational cohort study, comparing 4 cohorts with a follow-up of 3 years; each cohort exists of 40-55 patients to account for a 25% lost-to-follow-up-rate (e.g. by renal transplantation in the 3 dialysis groups, or by mortality).

### **Study population:**

- A. Patients with ESRD, 18-75 yr, who start treatment with nocturnal hemodialysis (5-7 times/week, 7-8 hr/night);
- B. Patients with ESRD, 18-75 yr, who undergo a living or cadaveric renal transplant;
- C. Patients with ESRD, 18-75 yr, treated with conventional hemodialysis (3-4 times/week, 3-5 hr);
- D. Patients with ESRD, 18-75 yr, treated with conventional peritoneal dialysis.

**“Intervention” (different modalities of renal replacement therapy, chosen by the patient, are observed):**

Group A: treatment with frequent nocturnal hemodialysis;

Group B: treatment with renal transplantation;

Group C: continuous treatment with hemodialysis;

Group D: continuous treatment with peritoneal dialysis.

**Main study parameters/endpoints:**

1. Change in coronary artery calcification score, per patient;
2. Change in pulse wave velocity, per patient.

**Nature and extent of the burden and risks associated with participation, benefit and group relatedness:**

- The study is an observational study, not an intervention-study.
- Participation does not influence or change the nature of the treatment, i.e. the modality of renal replacement therapy;
- Participation is associated with limited physical examination, questionnaires and blood sampling;
- Blood sampling is performed in combination with regular blood sampling, and requires a maximum of 20 cc blood per visit extra, once a year;
- Multislice CT-scan is performed at inclusion, and after 1, 2 and 3 years; this scan takes < 1 minute of time and radiation exposure is less than with conventional abdominal CT-scan; at inclusion and after 3 years, multislice CT-scan with intravenous contrast is performed to examine potential coronary stenosis.
- Yearly measurements of pulse-wave velocity are done with ultrasound (non-invasive), which takes 30 minutes of time.

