#### Investigations:

| time                                | incl | ½ yr | 1 yr | 1 ½ yr | 2 yr | 2 ½ yr | 3 yr |
|-------------------------------------|------|------|------|--------|------|--------|------|
| Multi-slice CT scan (MSCT) of heart | x    |      | x    |        | x    |        | x    |
| Coronary MSCT                       | x    |      |      |        |      |        |      |
| Pulse-wave velocity                 | x    |      | x    |        |      |        | x    |
| Lab assessments                     | x    | x    | x    |        | x    |        | x    |
| Weight/Blood pressure               | x    |      | x    | x      | x    | x      | x    |
| Medication                          | x    |      | x    |        | x    |        | x    |
| Quality-of-life                     | x    |      | x    |        | x    |        | x    |
| Karnofsky perf. status              | x    |      | x    |        | x    |        | x    |
| Clinical events                     |      |      | x    |        | x    |        | x    |
| continuously                        |      |      |      |        |      |        |      |

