#### 7.1.2 Secondary study endpoints

The secondary endpoints of the study are:

- change in pulse wave velocity
- change in coronary artery stenosis
- association between calcium, phosphate, PTH and change in coronary artery calcification score
- association between high-sensitivity-CRP, interleukin-6, interleukin-1, von Willebrand factor, myeloperoxidase, and change in coronary artery calcification score
- association between fetuin A, osteoprotegerin and matrix-Gla protein, and change in coronary artery calcification score
- cardiovascular events and mortality, assessed by the local investigator and the principal investigator separately

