#### Pulse wave velocity

Pulse wave velocity measurements will be performed at baseline and 1, 2 and 3 years after inclusion. It can be calculated from arterial pulse contours. These are obtained by applanation tonometry (Sphygmo-Cor system, PWV Inc, Sydney, Australia) at the carotid and radial arteries and femoral artery. With this technique the artery is pressed against a hard underground (bone) with a pencil-type probe. The probe contains a strain-gauge transducer at the tip with a small pressure-sensitive ceramic sensor area (Millar Instruments, Houston, Texas, USA). To determine aortic and brachial pulse wave velocity, the distance travelled by the pulse wave over the body surface is measured as the distance between the recording sites at the femoral or radial artery to the suprasternal notch minus the distance from the recording site at the carotid artery to the suprasternal notch, as described by others. The investigation takes about 15-20 minutes.

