#### Quality-of-life questionnaire

Patient's well-being will be assessed at baseline, 1, 2 and 3 years by the Kidney Disease Quality-of-Life Short Form. This questionnaire is validated for dialysis patients. Filling in the questionnaire takes about 15 minutes of time.

*The following procedures are part of standard medical treatment:*

Venipuncture at baseline and every 12 months, until 3 yr after inclusion. Venipuncture will be combined with venipuncture needed for routine care. Assessment of the routine tests (Hb, lipids, Ca, P, PTH) will be performed in the laboratory of the local treatment center. Assessment of the non-routine tests (inflammatory parameters, calcification inhibitors and serum calcification propensity) will take about 20 cc of blood per 12 month-visit, using sodium citrate and EDTA vacutainers. From February 2017 onwards, additional serum-separating vacutainers will be collected, in order to measure serum calcification propensity in active participants. A protocol concerning collection, processing and storage will be made separately under supervision of the Laboratory for Clinical Chemistry and Hematology Research, University Medical Center Utrecht.

Body weight is assessed at baseline and every 6 months, until 3 yr after inclusion. In transplant patients weight is measured at the ambulant visit. In dialysis patients, dry weight is obtained from the dialysis charts.

Blood pressure is assessed at baseline and every 6 months, until 3 yr after inclusion. In transplant patients and peritoneal dialysis patients, blood pressure is measured at the ambulant visit, in sitting position, by a sphygmomanometer. At least two readings are taken, separated by as much time as is practical; if readings vary by > 5 mmHg, additional readings are taken until two are close. In hemodialysis patients, blood pressure is taken before the hemodialysis session, again at least two readings as described above.

Medication is recorded at baseline and every 12 months, until 3 yr after inclusion: number and defined daily doses of antihypertensive drugs, number and defined daily doses of phosphate binders, number and defined daily doses of vitamin-D-analogues and calcimimetics, number and defined daily doses of immunosuppressive agents.

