#### 7.6 Follow-up of patients withdrawn from treatment

After withdrawal, follow-up is performed according to the study protocol as far as possible, as depicted in the following diagram, with different examples:

[figure not shown]

Example 1: when a patient treated with conventional hemodialysis receives a renal transplant after 1 ½ years, for this patient the study will end at 1 ½ years. Now all measurements, including calcium score and coronary MSCT and PWV will be done at 1 ½ years after inclusion, and within one month after the renal transplant.

Example 2: when a patient who is treated with peritoneal dialysis develops claustrophobic symptoms, follow-up is completed according to the study protocol, except for the MSCT.

Example 3: when a patient who is treated with a renal transplant and renal function deteriorates to a GFR less than 30 ml/min, follow-up will be done as planned apart from the coronary MSCT, because contrast medium cannot be given.

Example 4: when a patient treated with conventional hemodialysis receives a renal transplant before 1 ½ years, the patient is asked to participate again in the study; new baseline measurements will be performed, but the coronary MSCT will not be done at inclusion, nor after 3 years. In this case the total radiation exposure will not exceed than the exposure in the original study (maximum of 11.3 mSv).

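### The Section 3 schedule lacks the 3-year coronary CT and the 2-year pulse wave velocity that the text plans, so change in coronary stenosis has no scheduled follow-up scan

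*Protocol*

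**What the plan says.** **Coronary MSCT.** The Summary, under burden and risks, says that "at inclusion and after 3 years, multislice CT-scan with intravenous contrast is performed to examine potential coronary stenosis". Three of the examples in section 7.6 build on a repeat scan:

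- Example 1, a dialysis patient transplanted at 1½ years: "Now all measurements, including calcium score and coronary MSCT and PWV will be done at 1 ½ years after inclusion".
- Example 3 waives the coronary scan from later follow-up when graft function falls.
- Example 4, a patient who re-enters after an earlier transplant: "the coronary MSCT will not be done at inclusion, nor after 3 years".

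In the Section 3 Investigations table, the row "Coronary MSCT" has a mark under inclusion and none elsewhere. Section 7.3 describes the technique but gives no time points for it.

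**What depends on the repeat scan.** Section 7.1.2 lists "change in coronary artery stenosis" as a secondary endpoint. Secondary objective 1 compares progression of stenoses between the modalities, and objectives 2 to 4 also name progression of stenoses.

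**Pulse wave velocity.** Section 7.3: "Pulse wave velocity measurements will be performed at baseline and 1, 2 and 3 years after inclusion". The Summary also says yearly. The table has no mark at 2 years.

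**Laboratory, weight and blood pressure.** Section 7.3: "Venipuncture at baseline and every 12 months, until 3 yr after inclusion", with weight and blood pressure every 6 months. The table has a half-year mark for laboratory assessments and none for weight and blood pressure.

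**The concern.** A change needs two measurements. If the table is followed as it reads, a patient who completes 3 years has a baseline coronary scan and nothing to compare it with. The comparison of stenosis progression between the four modalities then has no data from the scheduled visits. A 3-year scan that was not made cannot be recovered at analysis.

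The table matters because, outside the Summary and the examples for patients who leave or switch, it is the only place in the protocol body that gives times for the coronary scan. The exposure assurance in Example 4 also depends on how many coronary scans the standard schedule contains.

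**Working it through.** **1. Time points side by side**

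| Measurement | Table, Section 3 | Text | Count for a completer, table / text |
|---|---|---|---|
| Calcium score MSCT | inclusion, 1, 2, 3 yr | same (Summary) | 4 / 4 |
| Coronary MSCT | inclusion | inclusion, 3 yr (Summary; Example 4) | 1 / 2 |
| Pulse wave velocity | inclusion, 1, 3 yr | baseline, 1, 2, 3 yr (7.3; Summary) | 3 / 4 |
| Laboratory | inclusion, ½, 1, 2, 3 yr | baseline and every 12 months (7.3) | 5 / 4 |
| Weight, blood pressure | inclusion, 1, 1½, 2, 2½, 3 yr | baseline and every 6 months (7.3) | 6 / 7 |

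The last two rows differ by one mark each, both at ½ year and in adjacent rows. A single mark moved by one row would explain both.

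**2. Consequence for the endpoints.** Under the table, the number of coronary scans after baseline at scheduled visits is 1 − 1 = 0. The only repeat scans left are those of Example 1, in dialysis patients who exit through transplantation. For pulse wave velocity the 2-year value is lost, while the difference between baseline and 3 years can still be computed.

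**3. Radiation figure.** Inputs from section 7.3: calcium score scan 0.8–1.2 mSv, coronary MSCT 2.5–4.1 mSv. The stated figure in Example 4 is 11.3 mSv. The protocol does not show how it was obtained. Assume that a re-entering patient has calcium scans at first inclusion, at 1 year, and at the new baseline and 1, 2 and 3 years (six scans), plus the one coronary scan at first inclusion. At the upper doses:

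- Re-entering patient: 6 × 1.2 + 1 × 4.1 = 7.2 + 4.1 = 11.3 mSv, which matches the stated figure.
- Standard schedule by the text: 4 × 1.2 + 2 × 4.1 = 4.8 + 8.2 = 13.0 mSv.
- Standard schedule by the table: 4 × 1.2 + 1 × 4.1 = 4.8 + 4.1 = 8.9 mSv.

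At the lower doses the same counts give 6 × 0.8 + 2.5 = 7.3 mSv, 4 × 0.8 + 2 × 2.5 = 8.2 mSv and 4 × 0.8 + 2.5 = 5.7 mSv. The ordering is the same.

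The ordering against the table does not depend on the dose. With one coronary scan in both schedules, the re-entering patient differs only by two additional calcium scans, so exposure is always higher than in the standard schedule.

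**The case against.** The strongest objection is that the table may not be at fault at all. It was read from a PDF by a program, and it shows signs of damage: the row for clinical events is split, and a half-year mark may have slipped between rows. A lost mark for coronary MSCT at 3 years or pulse wave velocity at 2 years cannot be excluded. The flow charts in Section 3 and the diagram in 7.6 are not visible and may show the repeat scan. This caveat stands, and it is why the first step is to look at the original. It does not remove the point, because the calcium score, medication, quality-of-life and Karnofsky rows read as intact while four other rows disagree with the text.

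A second objection is that the repeat scan is plainly intended: the Summary, Examples 1, 3 and 4, secondary objective 1 and the endpoint list all assume it. That is fair. A reader might infer from the table that the stenosis endpoint has been given up or ought to be deleted. The rest of the protocol does not support that.

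A reader might also infer that no patient at all would have a change in stenosis. That goes too far, because Example 1 gives an exit scan to dialysis patients who are transplanted. That subset is selected by the event of transplantation, has nobody from the transplant group, and cannot carry the four-group comparison.

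Finally, the radiation point is derivative. The scan count behind 11.3 mSv is a reconstruction, and under the text schedule the assurance holds (11.3 against 13.0 mSv).

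**Conclusion.** This is an internal inconsistency, and worth correcting. As the table reads, patients on scheduled visits have one coronary scan where the text plans two, and three pulse wave velocity measurements where the text plans four. With the table alone, secondary objective 1 and the stenosis endpoint have no 3-year measurement and cannot be assessed in the four-group comparison.

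The damage is limited. The primary endpoint keeps all four calcium score scans, and change in pulse wave velocity from baseline to 3 years survives with only the 2-year value missing. It would be wrong to infer that either of these endpoints is lost. The half-year discrepancies may be one displaced mark.

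The assurance that a re-entering patient's exposure stays within that of the original study holds with two coronary scans and fails with one. It would be wrong to call the assurance false outright, since that follows only if the table's row is the valid one. This part rests on the dose ranges in section 7.3 and on the assumed count of six calcium scans and one coronary scan.

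The conclusion as a whole rests on the table having been read correctly. Which schedule is right is not decided here.

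**What to change.** First, compare the machine-read table with the original page and with the flow charts, to see whether marks were lost or shifted. Then reconcile the coronary MSCT, pulse wave velocity, laboratory, and weight and blood pressure rows with the Summary and sections 7.3 and 7.6. After that, confirm that the schedule, the stenosis objective and endpoint, and the exposure statement in Example 4 agree, and show the scan count behind 11.3 mSv.

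If the original table proves to be complete and consistent, nothing needs to change there. Otherwise the cost is the correction of one table, a check of one dose total, and notification to the ethics committee as an amendment. The sample size and the primary analysis are not affected.
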